# Acute Effects of Cocoa Flavanols on Blood Pressure and Peripheral Vascular Reactivity in Type 2 Diabetes Mellitus and Essential Hypertension: A Protocol for an Acute, Randomized, Double-Blinded, Placebo-Controlled Cross-Over Trial

**DOI:** 10.3389/fcvm.2021.602086

**Published:** 2021-03-15

**Keywords:** type 2 diabetes, cocoa flavanols, vascular reactivity, blood pressure, muscular oxygenation, antihypertensive drugs

## Abstract

**Introduction:** Patients with type 2 diabetes mellitus are at high risk to develop vascular complications resulting in high morbidity and mortality. Cocoa flavanols are promising nutraceuticals with possible beneficial vascular effects in humans. However, limited research is currently available on the vascular effects in a diabetic population with inconsistent results. Possible reasons for this inconsistency might be heterogeneity in the given intervention (dose per time and day, single dose vs. split-dose, placebo formula) and the studied population (blood pressure at baseline, duration of diabetes, use of vasoactive antihypertensive and antidiabetic drugs, sex). Therefore, we aimed to develop a randomized, double-blinded, placebo-controlled cross-over trial to investigate whether cocoa flavanols have an acute impact on blood pressure and vascular reactivity in patients with type 2 diabetes with and without arterial hypertension.

**Methods and Analysis:** We will include participants in four groups: (i) patients with type 2 diabetes without arterial hypertension, (ii) patients with type 2 diabetes with arterial hypertension and 1 antihypertensive drug, (iii) non-diabetic participants with essential hypertension and 1 antihypertensive drug, and (iv) healthy controls. All participants will complete the same protocol on both testing days, consuming high-flavanol cocoa extract (790 mg flavanols) or placebo. Macrovascular endothelial function (flow-mediated dilation) and blood pressure will be measured before and after capsule ingestion. Forearm muscle vasoreactivity (near-infrared spectroscopy) and brachial artery blood flow (echo-doppler) will be assessed in response to a dynamic handgrip exercise test after capsule ingestion. Data will be analyzed with a random intercept model in mixed models.

**Clinical Trial Registration:**
www.Clinicaltrials.gov, identifier: NCT03722199.

## Introduction

Nitric Oxide, produced by the endothelial cells, is of crucial importance for general vascular health. It triggers relaxation of the vascular smooth muscle cells through accumulation of intracellular cyclic guanosine monophosphate (cGMP) (1–5).

Type 2 diabetes (T2DM) is the most prevalent type [90% (6, 7)] of diabetes mellitus, a highly prevalent disorder [estimated at 425 million people worldwide in 2017 and is expected to be 629 million in 2045 (8)] and poses a challenge to global health. It is characterized by chronic hyperglycemia, which increases oxidative stress. Free radicals easily bind with and simultaneously deactivate nitric oxide to form peroxynitrite. Both high amounts of oxidative stress and nitric oxide depletion increase the risk for developing micro- (retinopathy, nephropathy, and neuropathy) and macrovascular (cardiovascular, cerebrovascular, and peripheral artery diseases) complications (9, 10). These complications decrease quality of life and increase the global burden of T2DM in terms of health care costs, morbidity [hypertension is present in >60% of all patients with T2DM (11)], and even mortality (12–15). The past years researchers have been investigating products to limit or delay the onset of diabetic vascular complications with special attention for non-pharmacological approaches to counter polypharmacy.

Flavanols are promising nutraceuticals from the flavonoid family, a class of polyphenols (16), which can be found in several fruits, beans, teas, red wine, but predominantly in cocoa products (16, 17). Especial interest goes to flavanols derived from the seeds of the cocoa bean (*Theobroma cacao*), cocoa flavanols (CF), as they have higher antioxidant activity and more phenolic compounds (18). The increased attention for the effects of cocoa originates from research on the Kuna Indians. In contrast to migrated Kuna Indians to urban areas, Kuna Indians living on the San Blas Islands off the coast of Panama show low blood pressure (BP), even with increasing age, and have lower frequency of diabetes mellitus, cancer, and cardiovascular diseases (19). Causal research for this cardiovascular protection focused on environmental factors including nutrition and revealed that island-dwelling Kuna drink daily more than five cups of cocoa with high concentrations of flavanols and procyanidins (19–21). Starting from evidence based on further research on the vascular effects of CF, the European Food Safety Authority (EFSA) stated that CF help to preserve endothelium-dependent vasodilation in healthy populations, if taken in quantities exceeding 200 mg CF daily. This equals 10 g high-flavanol dark chocolate or 2.5 g high-flavanol cocoa powder (22).

The mechanisms of action of these CF are still debated. It is believed that they improve endothelial function (23), decrease BP (24), ameliorate insulin sensitivity (25–27), influence various inflammatory processes (28), and prevent platelet aggregation (29, 30) *via* antioxidant properties (31, 32), increasing nitric oxide bioavailability (33, 34), and inhibition of the angiotensin-converting-enzyme activity (35, 36). These effects seem to be induced, at least in part, by epicatechin, a highly active monomeric form of CF (37, 38).

It could be presumed that populations with T2DM could benefit from the intake of CF as it potentially reduces cardiovascular risk. CF would indeed improve both endothelial function and insulin sensitivity and so influence cardiovascular as well as metabolic disorders (39). Nonetheless, limited research with a high degree of inconsistency due to large heterogeneity (dose per time or day, acute or chronic intake, single dose vs. split-dose, placebo formula, and characteristics of population e.g., sex, BP at baseline, and use of vasoactive drugs like insulin and antihypertensives) is reported.

As presented in Table 1, at the moment, six studies investigated the effect of chronic CF intake (8 weeks−1 year) on vascular function (40–45) in patients with T2DM. Only two showed a statistically and clinically relevant decrease in BP (40, 45) and only two indicated a statistically improvement of endothelial function (41, 42) (Table 1). The heterogeneity of results about mid- to long-term effects of CF in patients with diabetes had been recently approached through a systematic review and meta-analysis (48). This paper indeed shows low quality of evidence of slight improvements in BP after mid/long-term CF ingestion. However, risk of bias, imprecision of the publications, and inconsistency and heterogeneity among the reports are reported and could be cause for the lack of a definite conclusion. This meta-analysis ultimately highlights the need for further research with a robust methodology taking into account possible confounding factors like hypertension at baseline and intake of BP lowering medication. Antihypertensive drugs, which were never considered in these papers on chronic effects of CF in patients with T2DM, have indeed a great impact on vasoreactivity (49) and may hence interfere with the effects of CF.

**Table 1 T1:** Characteristics of chronic and acute trials examining the effect of cocoa flavanols in patients with type 2 diabetes.

**References**	**Population (sex intervention group)/(sex control group)**	**Medication**	**Intervention**		**Control**		**Frequency and duration**	**Vascular assessment**
			**Form**	**Flavanol** ** content/d**	**Form**	**Flavanol content/d**		
**Chronic trials**								
Ayoobi et al. (40)	T2DM (14F + 7M)/ (13F + 10M)	Oral anti-DM drugs only, no information on anti-HT drugs	30 g 84% dark chocolate	No information	No intervention	No intervention	1x/d, 8 w	SBP↓, DBP ↓, NO =, angiotensin II =
Balzer et al. (41)	T2DM (13F + 8M)/ (16F + 4M)	Insulin allowed, anti-HT drugs allowed	Cocoa powder + 250 mL water	3 × 321 mg FL, 3 × 57.8 mg EC	Cocoa powder + 250 mL water	3 × 25 mg FL, 3 × 4.5 mg EC, matched for theobromine and caffeine	3x/d, 30 d	FMD ↓, MAP =, HR =
Curtis et al. (42)	T2DM, postmenopausal (47F)/(46F)	Insulin allowed, anti-HT drugs allowed	2 × 13.5 g flavonoid enriched chocolate	850 mg flavan-3-ols, 90 mg EC	2 × 13.5 g placebo chocolate	Matched for macronutrient content	2x/d (lunch + evening), 52 w	SBP =, DBP =, MAP =, PP = (PP variability ↓), CCA-IMT =, PWV ↓, AI =, ACE =, NO =, ET-1 =
Dicks et al. (43)	T2DM + HT (10F + 7M)/(7F + 11M)	Oral anti-DM drugs only, anti-HT drugs allowed	5 × 0.5 g cocoa powder capsules	207.5 mg flavanols, 40.4 mg EC, 13.6 mg C	5 × 0.5 g pure microcrystalline cellulose	No flavanols	3 in morning, 2 in evening, 12 w	SBP =, DBP=
Mellor et al. (44)	T2DM (5F + 7M)/(cross-over)	Oral anti-DM drugs only, anti-HT drugs allowed	3 × 15 g high polyphenol chocolate, 85% cocoa solids	16.6 mg EC	3 × 15 g low polyphenol chocolate, no non-fat cocoa solids	<2 mg EC, matched for macronutrient content	3x/d, 8 w	SBP =, DBP =
Rostami et al. (45)	T2DM + HT (20F + 12M)/(16F + 12M)	Oral anti-DM drugs only, anti-HT drugs allowed	25 g dark chocolate, 83% cocoa solids	450 mg flavonoids	White chocolate	No flavonoids	1x/d, 8 w	SBP ↓, DBP ↓
**Acute trials**								
Balzer et al. (41)	T2DM (2F + 8M)/(cross-over)	Insulin allowed, anti-HT drugs allowed	Cocoa powder + 250 mL water	*High*: 963 mg FL, 203 mg EC, 50.8 mg C *Medium*: 371 mg FL, 78.9 mg EC, 19.7 mg C	Cocoa powder + 250 mL water	75 mg FL, 16.8 mg EC, 4.2 mg C, matched for theobromine and caffeine	1x/d, 1, 2, 3, 4, 6 h post-intake	FMD ↓
Basu et al. (46)	T2DM + obese, (14F + 4M)/(cross-over)	Oral anti-DM drugs only, anti-HT drugs allowed	Cocoa powder + warm water, intake with a high-fat breakfast	480 mg FL, 40 mg EC, 18 mg C	Flavanol-free placebo powder + warm water, intake with a high-fat breakfast	<0.1 mg FL, not matched for theobromine or caffeine	1x/d, 30 min, 1, 2, 4, 6 h post-intake	SBP =, DBP =, large artery elasticity ↓, small artery elasticity =
Mellor et al. (47)	T2DM (1 postmenopausal F + 9M)/(cross-over)	Oral anti-DM drugs only, no information on anti-HT drugs	13.5 g high polyphenol chocolate + 200 mL water	3.5% polyphenols	13.5 g low polyphenol chocolate	0.9% polyphenols, identical formulation as intervention chocolate	1x/d, 3 h post-intake	Reactive hyperemia peripheral arterial tonometry ↓, endothelial serum adhesion molecules =

*The exact quantity of flavanols and/or epicatechin of the supplement is indicated only when this information is available in the paper; Effects in intervention group are expressed through: ↑, significant increase; ↓, significant decrease; =, no change; ACE, angiotensin-converting enzyme; AI, augmentation index at 75 heart rate; BP, blood pressure (systolic SBP, diastolic DBP); C, catechins; CCA-IMT, intima-media thickness of the common carotid artery; d, day; EC, epicatechins; ET-1, endothelin-1; F, female; FL, flavanols; FMD, flow-mediated dilation; h, hours; HR, heart rate; HT, hypertension; M, male; MAP, mean arterial pressure; min, minutes; NO, nitric oxide; PP, pulse pressure; PWV, pulse wave velocity; T2DM, Type 2 Diabetes Mellitus; w, weeks; y, year*.

The first step for profoundly testing these possible confounding factors would lie in the design of acute protocols applied to several well-characterized (particularly hypertension and its medications) groups of patients with T2DM. Up to now, three studies evaluated the vascular effects of acute CF supplementation in patients with T2DM (41, 46, 47). Two detected a significant improvement of endothelial function (41, 47) and one indicated a decrease in large artery elasticity (46) (Table 1). However, the same way as in the chronic studies, the three acute studies either gave no information about antihypertensive drugs or allowed the use of antihypertensive treatment (different types are reported) without considering this treatment as a possible confounding factor in the analyses (Table 1). To our knowledge, only four studies investigated the effect of CF when combined with antihypertensive drugs (different types are reported) in non-diabetic hypertensive adults (50, 51), in non-diabetic heart transplant recipients (52), and in non-diabetic adults with congestive heart failure (53). These showed a supplementary effect of cocoa intake on BP (50, 51) and/or endothelial function (50, 52, 53).

In addition, together with the heart, the micro- and macrocirculation determine the hemodynamics of the circulating system (54). It is important to study both systems simultaneously, but apart from one report (46) none of these studies in patients with T2DM investigated the effect of CF simultaneously in both of these vascular beds (i.e., micro and macrovascular beds) (Table 1).

In this study, we will take into account these results, assumptions, and points of heterogeneity as will be explained in this paper. In addition, this study will investigate the impact of CF on both micro- and macrovascular functions. As CF would increase nitric oxide, we hypothesize more effect on macrovessels as microvessels are also dependent on other vasodilators like prostaglandins. However, as little is known so far, our research will provide novel insights on this matter. Moreover, acute protocols will help to be sure of the efficacy of the dose chosen, to know which of the vascular (either micro or macrovascular) beds would be more impacted, and to identify whether some patients would be non-responders because of their medications. Hence, since our study has a robust methodology, it may act as a sort of “pilot” for the setup of long-term trials.

This acute, randomized, double-blinded, placebo-controlled cross-over study aims to investigate whether a single intake of a high dose of CF (790 mg flavanols) induces an improvement in endothelial function (primary outcome), a reduction in BP, and an enhancement in muscle vasoreactivity and oxygenation in patients with T2DM compared to healthy controls.

Because hypertension is a common comorbidity in patients with T2DM and as little is known so far concerning possible interferences between antihypertensive drugs and CF actions especially in patients with diabetes mellitus, this study will additionally investigate possible influence of beta-blockers (BB), angiotensin converting enzyme inhibitor (ACEi), or angiotensin receptor blocker (ARB) in diabetic persons with arterial hypertension and non-diabetic persons with essential hypertension treated with these drugs.

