### Participants

#### Eligibility Criteria

All subjects are divided in four groups: (i) patients with T2DM with arterial hypertension (with BB, *n* = 5/ACEi, *n* = 5/ARB, *n* = 5) (*n* = 15), (ii) patients with T2DM without arterial hypertension (*n* = 10), (iii) non-diabetic patients with essential arterial hypertension (BB, *n* = 10/ACEi, *n* = 10/ARB, *n* = 10) (*n* = 30), and (iv) healthy participants (control group; *n* = 20).

Inclusion and exclusion criteria are summarized in Table 2.

**Table 2 T2:** In- and exclusion criteria for participants in this study.

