**Inclusion criteria**
Male and female; age: 18–85 years; BMI: 20–40 kg/m^2^
(i) Patients with T2DM without arterial hypertension: at least 5 years T2DM [HbA1c ≥6.5%, glucose (fasting) ≥126 mg/dl, glucose (not fasting): ≥200 mg/dl, defined by the American Diabetes Association (ADA) (55)]
(ii) Patients with T2DM with arterial hypertension: at least 5 years T2DM [HbA1c ≥6.5%, glucose (fasting) ≥126 mg/dl, glucose (not fasting): ≥200 mg/dl, defined by the American Diabetes Association (ADA) (55)] AND at least 1 year arterial hypertension taking BB, ACEi or ARB (optionally combined with diuretics)
(iii) Patients with essential arterial hypertension: at least 1 year arterial hypertension taking BB, ACEi or ARB (optionally combined with diuretics), matched by age, sex, and BMI with subjects with T2DM
(iv) Healthy controls: taking no medication except for contraceptive drugs, matched by age, sex, and BMI with subjects with T2DM

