**Exclusion criteria**
Smoking habits: current smoking; smoking history of more than 30 years or pack years are higher than years of smoking cessation
Alcohol consumption: more than 10 units per week
Additional systemic disorders: chronic inflammatory disease, active cancer
Microvascular complications: retinopathy, nephropathy, peripheral sensory(motor), or autonomic neuropathy
Macrovascular complications: cardiovascular and respiratory diseases: heart failure NYHA class 3 and 4, uncontrolled arrhythmias or angora, documented peripheral arterial disease or experienced heart attack, active or chronic recurrent vasculitis, severe to very severe chronic pulmonary diseases (GOLD stage III and IV)
Neurological diseases: cerebrovascular accident, transient ischemic attack, reversible ischemic neurological deficit or stenosis >50% by doppler
Other: important (and relevant) musculoskeletal disorders; factors that impede the execution of the dynamic handgrip exercise test; pregnancy; known cognitive impairment (such as dementia, intellectual disability), language barriers
Medication: medication directly influencing endothelial function except for insulin or antihypertensive drugs; nitric oxide-containing medication; phosphodiesterase type 5-inhibitors

*T2DM, type 2 diabetes mellitus; BMI, body mass index; BB, beta blocker; ACEi, angiotensin converting enzyme inhibitor; ARB, angiotensin receptor blocker*.

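### Drug effects on cocoa flavanol response cannot be separated from hypertension in this design, so it cannot support the stated hope of finding medication-related non-responders

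*Protocol article*

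**What the plan says.** - **Introduction.** In explaining what acute protocols offer, the article says they will help "to identify whether some patients would be non-responders because of their medications". The last paragraph adds an aim: "this study will additionally investigate possible influence of beta-blockers (BB), angiotensin converting enzyme inhibitor (ACEi), or angiotensin receptor blocker (ARB". It places that aim in hypertensive people, with and without diabetes, who are treated with these drugs.
- **Eligibility Criteria.** Four groups are planned: type 2 diabetes (T2DM) with hypertension (15; 5 per drug class), T2DM without hypertension (10), essential hypertension without diabetes (30; 10 per class) and healthy controls (20).
- **Table 2, inclusion.** Both hypertensive groups need "at least 1 year arterial hypertension taking BB, ACEi or ARB (optionally combined with diuretics". For the controls the entry is "Healthy controls: taking no medication except for contraceptive drugs". For T2DM without hypertension nothing is said about antihypertensives.
- **Table 2, exclusion.** The barred medication is "medication directly influencing endothelial function except for insulin or antihypertensive drugs", so antihypertensive use is not expressly ruled out in the normotensive T2DM group.
- **Guidelines for Participants.** Usual medication continues on study days, with antihypertensives taken two hours before the start.
- **Data-Analysis Plan.** The interactions are group × supplementation and time × supplementation. Medication intake is considered as a covariate. There is no drug class × supplementation term and no definition of a responder.

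**The concern.** The article's own review of earlier work names baseline hypertension and blood-pressure-lowering medication as possible confounders and faults earlier trials for ignoring antihypertensive treatment. The planned groups then tie the two factors together: to be hypertensive in this trial is to be on a BB, ACEi or ARB, and no group is recruited to be one without the other.

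If CF does less in the hypertensive groups, hypertension itself, the drugs, or both could be the cause, and the data could not say which. The study is offered as a kind of pilot for long-term trials and as possible input to practice guidelines. A statement that a drug interferes with CF, if drawn from that group contrast, would carry into both without support.

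**Working it through.** **1. Planned layout** (Eligibility Criteria, Table 2)

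| | On BB, ACEi or ARB | Not assigned any |
|---|---|---|
| Hypertensive | 15 + 30 = 45 | 0 |
| Normotensive | 0 planned | 10 + 20 = 30 |

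The total is 75. Because medication continues at both visits, drug status does not vary within a person either, so the cross-over adds no information on it.

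**2. What the group contrast estimates.** Let θ be the CF-minus-placebo effect in a normotensive untreated group, *a* the shift in that effect due to hypertension, and *b* the shift due to the drug.

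- Normotensive group: θ
- Treated hypertensive group: θ + *a* + *b*
- Difference: *a* + *b*

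This holds in the diabetic stratum (15 v 10) and the non-diabetic stratum (30 v 20). The pairs (*a*, *b*) = (δ, 0) and (0, δ) give the same expected data for any δ and any sample size.

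**3. Rank check on the 75 planned participants**, for the within-person CF effect

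| Terms | Columns | Rank |
|---|---|---|
| Intercept, diabetes, hypertension, diabetes × hypertension | 4 | 4 |
| The same plus any antihypertensive | 5 | 4 |
| First row plus three class indicators against no drug | 7 | 6 |
| First row plus two class-versus-class contrasts | 6 | 6 |

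An overall drug effect is not estimable. Differences between classes are.

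**4. What the written model delivers.** Group has four levels and class is not one of them. Medication as a covariate shifts the level of the outcome, not the CF effect. So the only contrast in CF effect related to hypertension or drugs is the one in step 2. The estimable class contrast is not among the listed terms.

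**5. Precision of the class contrast.** The article gives no SD. It cites 20–30 participants for a detectable change of 1.5–2% FMD (80% power, alpha 0.05). Assuming a two-sided paired comparison, n = (SD × 2.80 / δ)², so SD = δ√n / 2.80:

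- lowest: 1.5 × √20 / 2.80 = 2.4
- highest: 2 × √30 / 2.80 = 3.9

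The detectable difference between two classes is 2.80 × SD × √(1/n₁ + 1/n₂):

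| Comparison | SD 2.4 | SD 3.9 |
|---|---|---|
| T2DM, 5 v 5 | 4.2 | 6.9 |
| Essential hypertension, 10 v 10 | 3.0 | 4.9 |
| Pooled, 15 v 15 | 2.4 | 4.0 |

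Power for a 2-point difference at 15 v 15 is 63% down to 29%. The separate statement of a minimum of nine per group cannot be reproduced, because its effect size and SD are not given; it does not bear on this point.

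**6. Individuals.** One person's observed CF-minus-placebo difference is the true individual response plus the error of two single days. With one day of each there is no replicate from which to separate the two parts, so no individual can be classified.

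**The case against.** The strongest reply is that the added aim is set inside the hypertensive groups and that equal class cells (5/5/5 and 10/10/10) suit a between-class comparison, which is free of the aliasing. That stands in part: the layout does support that comparison. But the Data-Analysis Plan lists no class × supplementation term. Even with one, the comparison shows only whether classes differ. Without an untreated hypertensive reference it cannot show that any class blunts CF, and an effect common to all three stays merged with hypertension. Class was also not randomised, and added diuretics are allowed.

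Three stronger readings are tempting, and the article does not support them:

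- *The trial plans to attribute non-response to drugs.* A reader might infer this from the Introduction, but the wording there is that acute protocols will help in identifying such patients. The analysis section contains no attribution rule and no individual classification.
- *Hypertension and drug use are exactly the same variable in all 75.* This is true of the plan, but Table 2 does not bar antihypertensives in the 10 normotensive T2DM patients. If, say, 5 of them took one, the drug term would become estimable (rank 5 of 5). It would then rest on a few incidental users and on assuming the same drug effect with and without hypertension. The plan neither recruits for this nor relies on it.
- *A false drug effect of some given size will be reported.* The article gives no figure for how hypertension shifts the CF effect on FMD, so no size or direction can be stated.

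It is also fair to say that a condensed article may leave limitations to other documents. The point here is that the article states a capability which the stated design lacks.

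**Conclusion.** The concern holds in this limited form. As planned, the contrast in CF effect between the 45 treated hypertensive and 30 normotensive participants identifies only the sum of a hypertension effect and a drug effect, and a larger sample would not change that. Individual non-responders cannot be identified from one day on each supplement. The between-class contrast is estimable but observational, small, and missing from the listed model terms.

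This rests on the normotensive T2DM group being essentially free of antihypertensives, as the group structure implies. The precision figures also assume a two-sided test and an SD of 2.4–3.9 implied by the cited sample sizes; the aliasing depends on neither.

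The damage is confined to the additional aim. The randomised CF-versus-placebo comparison within each group, including its use for the primary FMD outcome, is untouched. The point is worth acting on because the correction is nearly free.

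**What to change.** 1. Describe hypertensive-versus-normotensive differences in CF effect as differences by treated hypertension, not by drug.
2. Base any statement on drugs only on the BB versus ACEi versus ARB contrast in CF effect among hypertensive participants. Add a drug class × supplementation term for this, report it with confidence intervals, and label it exploratory and observational. State that, without an untreated hypertensive reference, it shows only whether classes differ, not that a class blunts CF.
3. Delete the claim about identifying non-responders because of medication.

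Do not adjust the class contrast for pre-intake blood pressure. It is measured after the antihypertensive has been taken, so it is partly a result of the drug, and adjustment could remove some of the influence under study.

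The cost is wording plus one exploratory model term, with no new participants or measurements. The downside is a narrower claim about drugs.

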### Statistical Analyses

#### Power and Sample Size Calculation

Sample size calculations are based on previous research focusing on interventional studies with FMD measurements (77, 78) who established that in cross-over trials at least 20–30 participants are required for a minimal detectable change of 1.5–2% in FMD (80% power, alpha-level = 0.05). Sample size calculation was done by SAS power and sample size, indicating a minimum of nine participants in each group (41). Data will be analyzed taking into account volunteer- and methodology-related factors (79).

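### The stated model has no drug class × supplementation term, so it does not estimate the influence of beta-blocker, ACEi or ARB on the cocoa-flavanol effect that the additional aim asks about

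*Protocol article*

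**What the plan says.** **Aim.** The Introduction gives as its reason that "little is known so far concerning possible interferences between antihypertensive drugs and CF actions especially in patients with diabetes mellitus". It then states that "this study will additionally investigate possible influence of beta-blockers (BB), angiotensin converting enzyme inhibitor (ACEi), or angiotensin receptor blocker (ARB") in diabetic and non-diabetic people with hypertension treated with these drugs. Earlier in the Introduction, one purpose of an acute design is "to identify whether some patients would be non-responders because of their medications".

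**Recruitment.** Eligibility Criteria sets quotas by class in two of the four groups: "patients with T2DM with arterial hypertension (with BB, *n* = 5/ACEi, *n* = 5/ARB, *n* = 5) (*n* = 15") and "non-diabetic patients with essential arterial hypertension (BB, *n* = 10/ACEi, *n* = 10/ARB, *n* = 10) (*n* = 30"). The other two groups are type 2 diabetes without hypertension (10) and healthy controls (20).

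**Model.** The Data-Analysis Plan specifies a random-intercept mixed model. Its fixed effects are group, supplementation and time, and its two interactions are group × supplementation and time × supplementation. Medication intake is named once, in the list of covariates.

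**Size.** Power and Sample Size Calculation cites 20–30 participants for a detectable change of 1.5–2% in FMD in cross-over trials (80% power, alpha 0.05). It then reports its own calculation as "indicating a minimum of nine participants in each group (41").

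**Co-medication.** The Abstract describes the hypertensive groups as on a single antihypertensive drug. Table 2 admits patients "taking BB, ACEi or ARB (optionally combined with diuretics").

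**The concern.** Interference of a drug class with cocoa flavanols means that the flavanol-minus-placebo difference varies by class. Only a term that crosses class with supplementation can show this. The plan recruits by class but does not carry class into the treatment contrast. Followed as written, the analysis would end without an estimate for the aim that the class quotas serve.

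The Introduction criticises earlier acute trials in type 2 diabetes for not considering antihypertensive treatment as a possible confounder in their analyses, and it offers this trial as a kind of pilot for long-term work. Without a pre-specified class analysis, any statement about drug classes would come from an analysis chosen after the fact, partly in very small cells.

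**Working it through.** **1. What the stated model estimates**

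For participant i under supplement s (flavanol or placebo), post-intake:

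Y(i,s) = intercept + group + supplement(s) + group × supplement(s) + c·medication(i) + random intercept(i) + error

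Guidelines for Participants asks each person to take the usual prescribed medication, so medication(i) is the same at both visits. Subtracting placebo from flavanol gives:

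Y(i,CF) − Y(i,placebo) = supplement effect + group-specific supplement effect + error difference

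The term c·medication(i) cancels, as does the random intercept. Time × supplementation brings in the pre/post change but does not involve medication. Group × supplementation lets the effect differ between the four groups, but each hypertensive group holds all three classes. Within the four groups, antihypertensive treatment also cannot be separated from hypertension itself. No coefficient in the model is the influence of class on the flavanol effect.

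**2. The plan's own size figure**

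The minimum of nine cannot be reproduced, because the article gives no SD, within-person correlation or effect size for it. The four groups (15, 10, 30, 20; total 75) all meet it. By drug class, the diabetic cells are 5 and the non-diabetic cells 10. Pooled over diabetes status each class has 5 + 10 = 15, so 3 × 15 = 45 hypertensive participants, with the same diabetic share (5 of 15) in every class.

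**3. Precision (assumptions: two-sided 0.05, 80% power, noncentral t, equal SDs)**

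Standardised effect d needed for 80% power:

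- Paired, within a class: 1.682 (n = 5), 1.067 (n = 9), 0.996 (n = 10), 0.778 (n = 15), 0.660 (n = 20), 0.529 (n = 30).
- Two classes compared on within-person differences: 2.024 (5 v 5), 1.325 (10 v 10), 1.060 (15 v 15).

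*Basis A: 20–30 participants detect 1.5–2 points.* Implied SD of the paired difference = change / d:

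- 1.5 / 0.660 = 2.27 and 2.0 / 0.660 = 3.03 (n = 20)
- 1.5 / 0.529 ≈ 2.83 and 2.0 / 0.529 = 3.78 (n = 30)

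The article does not say which n goes with which change, so the full range 2.3–3.8 applies. Detectable difference = d × SD:

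| Comparison | d | FMD points |
|---|---|---|
| Within class, n = 5 | 1.682 | 3.8–6.4 |
| Within class, n = 10 | 0.996 | 2.3–3.8 |
| Within class, n = 15 | 0.778 | 1.8–2.9 |
| Between classes, 5 v 5 | 2.024 | 4.6–7.7 |
| Between classes, 10 v 10 | 1.325 | 3.0–5.0 |
| Between classes, 15 v 15 | 1.060 | 2.4–4.0 |

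*Basis B: nine participants give 80% power, so d = 1.07.* Power for an effect of that size within a class is 44% at n = 5 and 85% at n = 10. Power for a between-class difference of that size is 32% (5 v 5), 62% (10 v 10) and 80% (15 v 15).

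On both bases the diabetic cells alone are too small for inference. Pooled classes of 15 support an exploratory estimate, but a between-class contrast reaches 80% power only on the more optimistic basis B.

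**The case against.** **The aim is secondary and softly worded, and detail may sit in an SAP.** The article speaks of a possible influence, investigated additionally, which is already close to exploratory. Group × supplementation does bear on it, since it contrasts diabetes with and without treated hypertension. This limits the weight of the point. It does not remove it: the contrast is confounded with hypertension and does not separate the classes. The article also lists its interactions explicitly and gives medication another role, so this is a stated model that does not match a stated aim.

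**The minimum of nine.** A reader might infer that cells of 5 breach the plan's own minimum. They do not. Nine is stated per group, and all four groups meet it. The diabetic cells fall below nine only if drug class is made the unit of inference, and the non-diabetic cells of 10 exceed it even then.

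**Non-responders.** A reader might take this wording as a plan to classify individuals from one flavanol and one placebo visit. It reads more naturally as a difference by medication, and nothing in the Data-Analysis Plan classifies individuals.

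**Tests in cells of 5.** A reader might expect claims of no flavanol effect under a given drug from five people. No section plans such tests. The risk arises only because no class analysis is specified.

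**Conclusion.** The point holds as a mismatch between aim and model: the additional aim and the class quotas call for a drug class × supplementation estimate, and the stated model contains none. This part needs no numerical assumption beyond each participant's medication being the same at both visits.

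It would be too strong to say that the trial cannot address the aim. The crossover data on 45 hypertensive participants allow an exploratory answer once the term is added. How precise that answer is depends on an SD that the article does not give. The ranges above assume two-sided tests, equal SDs and either the 20–30 or the nine-participant statement as the basis. Drug class is not randomised, so even a well-estimated class difference could reflect the kind of patient given each drug. The primary comparison is unaffected. The change should be made, but it is not a fatal flaw.

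**What to change.** Before unblinding, pre-specify one further model in the 45 hypertensive participants:

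- Fixed effects: drug class, supplementation and drug class × supplementation, with diabetes status as a factor. For outcomes measured before and after intake, extend the interaction to × time.
- Report the flavanol-minus-placebo effect per class (n = 15 pooled) and the between-class differences, each with a 95% CI. Label them exploratory and state that drug class is not randomised.
- Present the diabetic cells of 5 descriptively, without tests.
- Use diuretic co-medication only in a sensitivity analysis. A further diuretic interaction is too much for 45 people.
- State the assumed SD of the paired difference, so that readers can judge precision.

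Separately, reconcile the Abstract's description of a single antihypertensive drug with the diuretic allowance in Table 2.

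Cost: one extra pre-specified model and more modest wording on drug classes.
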